**Methods:**

The dose-escalated hypoxia-adjusted radiotherapy trial is an open-label, parallel, randomised, single-centre, phase II study. Patients with HNC will undergo [18F]. FMISO PET CT to identify hypoxic regions. Normoxic patients will be labeled as Arm 1 and will not be part of the primary assessment. Patients with hypoxia will be stratified into two arms (2 and 3). Arm 2 will receive standard radiotherapy of 70 Gy in 2 Gy fractions, while Arm 3 will receive an additional boost to the hypoxic sub-volumes, delivering a total of 80 Gy (Phase 2). All patients in Arms 2 and 3 will also receive concurrent chemotherapy with cisplatin. Patients will be monitored weekly for treatment tolerance, with acute adverse events recorded according to National Cancer Institute Common Terminology Criteria for Adverse Events v5.0. The primary endpoint is LRC, defined as the time from randomisation to the first histopathologically confirmed relapse of locoregional disease. Secondary endpoints include OS, locoregional relapse-free survival, acute and late toxicity and patient-reported outcomes assessed using the European Organisation for Research and Treatment of Cancer QLQ-C30 and QLQ-H&N35 questionnaires.

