## Intervention

All patients will be treated using IMRT (with pre-specified image guidance protocol as per institutional standards).

## Arm 1

Patients will receive standard care and serve as external controls, representing typical clinical practice. Their cases will be reviewed in the head and neck multidisciplinary clinic, following the institutional approach. These patients will undergo treatment analogous to that of ‘Arm 2,’ but with allowances for protocol deviations at the discretion of the treating radiation oncologist.

## Arm 2

The prescribed radiotherapy dose will be 70 Gy, delivered in daily fractions of 2 Gy. The elective volume will receive 50 Gy, administered in 2 Gy daily fractions over the first 5 weeks. This will be followed by a boost to the high-risk volume, delivering an additional 20 Gy in 2 Gy daily fractions over the subsequent 2 weeks. The entire treatment will be delivered in a phased approach using sequential planning.

## Arm 3

The radiation dose will be similar to ‘Arm 2’. In addition, the HSV identified on baseline FMISO scans will be contoured and an isotropic margin of 3 mm will be given. This volume will be boosted in phase II to a total dose of 80 Gy. (Addition of 30 Gy in 3 Gy daily fraction added in phase II as a simultaneous integrated boost – SIB) (Figure 2). The BED and EQD2 for Arm 3 (to HSV) are 99 Gy_10_ and 82.5Gy, respectively, in comparison to 84 Gy_10_ and 70 Gy, respectively, in Arm 2.

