## Adherence to protocol and concomitant care

Patients will be monitored weekly to assess their tolerance to treatment. Any patient exhibiting grade 3 or higher toxicity will require urgent therapeutic intervention. The most anticipated side effects are mucositis and dysphagia. Patients will be evaluated weekly for the need for nutritional support and feeding tube placement, as well as on an as-needed basis. In rare instances of severe toxicities not responding to conservative measures, a treatment break may be necessary. The resumption of radiotherapy will be contingent upon the resolution of major toxicities, with the aim of restarting radiotherapy as soon as clinically feasible.

Outcome measures: Oncological outcomes will be collected by a designated team of head and neck specialists (radiation oncologist, surgeon and radiologist)

Response assessment*:* The patients would be assessed for the first time after 12 weeks of completion of definitive radiotherapy. The patients would be assessed by 18-FDG PET CT (± MRI) and direct laryngoscopy. The need for biopsy versus repeat imaging at a short interval will be taken by a multispeciality clinic taken into view the clinical examination, laryngoscopy findings (including narrow band imaging) and radiological findings.

*Primary endpoint: locoregional control* (LRC): LRC is defined as the absence of tumour recurrence or progression within the primary tumour site and the regional lymph nodes, as determined by clinical evaluation, imaging studies and/or biopsy confirmation. LRC will be assessed at predefined time points, with the primary time point being 2 years post-treatment. Locoregional recurrence within 2 years post-treatment is associated with significant morbidity and reduced quality of life. Therefore, 2-year LRC serves as a clinically meaningful endpoint to guide treatment decisions and optimise outcomes for patients receiving escalated radiation doses.

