### Secondary endpoints

*Overall Survival (OS)*: The duration of OS is defined as the time from the date of randomisation to death from any cause. If there is no death, the OS duration will be censored at the time of analysis.

*Locoregional relapse-free survival (LRFS)*: LRFS is defined as the time from the date of randomisation to the first histopathologically confirmed relapse of locoregional disease. If there is no confirmed recurrence, the LRC duration will be censored at the time of analysis. Death from any cause will be considered as an event in LRFS.

*Acute toxicity:* Acute adverse events will be assessed and recorded according to the NCI CTCAE version 5.0 [40]. Evaluations will be conducted at baseline, mid-treatment (week 4), immediately post-treatment, 2 weeks post-radiotherapy and subsequently at 3 months post-treatment.

*Late toxicity assessment*: Long-term toxicities of the upper aerodigestive tract will be recorded at 1 and 2-year follow-ups. They will be assessed using the RTOG long-term toxicity assessment [41].

*Patient-reported outcome*: The data will be collected by the trial coordinator and, research nurse by collecting proformas filled by patients.

European Organisation for Research and Treatment of Cancer (EORTC) head and neck questionnaires: The Hindi versions of the EORTC QLQ-C30 [42] and QLQ-H and N35 questionnaires [43, 44] will be obtained from the QoL unit, EORTC Data Centre in Brussels, Belgium. The EORTC QLQ-C30 questionnaire consists of five functional scales that include physical, role, cognitive, emotional and social; three symptom scales that include fatigue, pain and nausea/vomiting; a global QoL scale; and six single items that include dyspnea, insomnia, appetite loss, constipation, diarrhoea and financial difficulties. The QLQ-H and N 35 questionnaires consisted of seven multiple-item scales that assess the symptoms of pain, swallowing ability, senses (taste/smell), speech, social eating, social contact and sexuality and six single-item scales that assess the presence of symptomatic problems associated with teeth, mouth opening, dry mouth (xerostomia), sticky saliva, coughing and feeling ill. All the scales of the EORTC QLQ-C30, QLQ-H and N35 range from 0 to 100.

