**Figure 2. figure2:**
[figure not shown]
(a–c) shows 18F FDG PET CT images in axial, coronal and sagittal views, respectively. (d–f) shows 18F FMISO PET CT images in axial, coronal and sagittal views, respectively. (g–i), target delineation as labeled in axial, coronal and sagittal views, respectively. GTV – Gross Tumour Volume, HSV – Hypoxic Sub-Volume, Ph I 50 Gy – Volume receiving 50 Gy in 25 fractions in phase 1, Ph II 20Gy – Volume receiving 20 Gy in 10 fractions in phase 2. Ph II 30Gy – Volume receiving 30 Gy in 10 fractions in phase 2.

**Table 1. table1:** Schedule of enrolment, interventions, and assessments for the DEHyART study as per SPIRIT guidelines.

Time points	Study period														
	Enrolment	Allocation	Post allocation (During RT)								Acute phase (Post RT)		Late phase (Post RT)		
	Pre RT	Pre RT	Week								Month		Month		
			1	2	3	4	5	6	7	Post RT 2	3	6	12	18	24
Enrolment															
Eligibility screen	X														
Informed consent	X														
Diagnostic/staging workup	X														
CCI	X														
F MISO PET CT (baseline)	X														
Allocation															
Randomisation		X													
Intervention															
Arm 1 (CRT)			X	X	X	X	X	X	X						
Arm 2 (CRT)			X	X	X	X	X	X	X						
Arm 3 (CRT)			X	X	X	X	X	X	X						
Dose escalation (Arm 3)							X	X	X						
Second F MISO PET CT (Arm 3)						X									
Assessment															
CTCAE v5 (acute toxicity)		X				X			X	X	X	X			
EORTC QLQ C30 and HN35		X				X			X	X	X	X	X	X	X
MDADI		X				X			X	X	X	X	X	X	X
RTOG (late toxicity)													X	X	X
Response assessment (Clinical ± radiological)											X	X	X	X	X

**Table 2: table2:** Inclusion and exclusion criteria for enrolment in DEHyART study.

Inclusion criteria	Exclusion criteria

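### Acute toxicity is scheduled for CTCAE grading only at weeks 4 and 7 of radiotherapy, although patients are reviewed weekly and the abstract can be read as weekly CTCAE recording

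*Protocol article*

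**What the plan says.** The acute toxicity endpoint (Secondary endpoints) uses CTCAE version 5.0 and fixes its time points: "Evaluations will be conducted at baseline, mid-treatment (week 4), immediately post-treatment, 2 weeks post-radiotherapy and subsequently at 3 months post-treatment".

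Table 1, read by column position, marks CTCAE at allocation, week 4, week 7, 2 weeks after radiotherapy, month 3 and month 6. Month 6 is not in the text.

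The section on adherence and concomitant care sets a denser contact schedule: "Patients will be monitored weekly to assess their tolerance to treatment". It also makes care depend on grade: "Any patient exhibiting grade 3 or higher toxicity will require urgent therapeutic intervention".

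The abstract (Methods) puts review and recording in one sentence: "Patients will be monitored weekly for treatment tolerance, with acute adverse events recorded according to National Cancer Institute Common Terminology Criteria for Adverse Events v5.0".

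On timing, the Arm 2 paragraph under Intervention says of phase I: "The elective volume will receive 50 Gy, administered in 2 Gy daily fractions over the first 5 weeks". The high-risk boost follows, "delivering an additional 20 Gy in 2 Gy daily fractions over the subsequent 2 weeks". The Arm 3 paragraph adds the hypoxic sub-volume boost in phase II. The dose-escalation row of Table 1 marks weeks 5, 6 and 7.

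**The concern.** The Sample size section names preliminary safety as an aim, and acute toxicity is a listed secondary endpoint. The useful information is what happens once the arms diverge, which is at the boost. The first on-treatment grade comes before that, and the second comes at the end of treatment. A severe episode that arises and settles between them is seen in clinic but has no scheduled place in the endpoint data.

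No other stated route clearly collects such an episode. The oversight section sends unexpected or grade 5 toxicity to the SAE committee. Mucositis and dysphagia are named as the most anticipated effects, so a grade 3 or 4 episode of either need not qualify. Treatment breaks, which the protocol expects to be rare, add to this: radiotherapy resumes only once major toxicity has resolved, so the episode that caused the break may be over by the next scheduled grade.

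The documents also leave open which data set will exist. Staff who follow the abstract would record CTCAE weekly; staff who follow the endpoint text or Table 1 would record it at set points. In an open-label trial, unscheduled extra grading could also differ between arms.

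**Working it through.** **Treatment timeline** (inputs from Intervention; 5 fractions per week follows from the stated doses and weeks)
- Phase I: 50 Gy / 2 Gy = 25 fractions; 25 / 5 = 5 weeks, so weeks 1-5.
- Phase II: 20 Gy / 2 Gy = 10 fractions; 10 / 5 = 2 weeks, so weeks 6-7.
- The first boost fraction is number 26, in week 6. This reproduces the timeline in the text.
- By the end of week 4 a patient has had at most 4 × 5 = 20 fractions, or 40 Gy, with the same planned dose in both arms. This also holds if the boost starts in week 5, as Table 1 marks it.

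**Grades against weeks**

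| Week | 1 | 2 | 3 | 4 | 5 | 6 | 7 |
|---|---|---|---|---|---|---|---|
| Weekly review | yes | yes | yes | yes | yes | yes | yes |
| Scheduled CTCAE | no | no | no | yes | no | no | yes |
| Boost, Intervention text | no | no | no | no | no | yes | yes |
| Boost, Table 1 | no | no | no | no | yes | yes | yes |

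Scheduled grades cover 2 of 7 weekly reviews, leaving 7 − 2 = 5 uncovered. Boost weeks without a scheduled grade: 1 of 2 by the text (week 6), 2 of 3 by Table 1 (weeks 5 and 6).

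**Which episodes fall between the grades**
This is an illustration, not an estimate. The documents give no episode lengths, so I assume whole-week episodes that are equally likely to start in any of weeks 1-7, with each evaluation recording the current grade only.

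| Episode length | Start weeks missed | Share missed | Missed starts in boost, text (weeks 6-7) | Missed starts in boost, Table 1 (weeks 5-7) |
|---|---|---|---|---|
| 1 week | 1, 2, 3, 5, 6 | 5/7 = 71% | week 6 | weeks 5 and 6 |
| 2 weeks | 1, 2, 5 | 3/7 = 43% | none | week 5 |
| 3 weeks | 1 | 1/7 = 14% | none | none |

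The grade 2 weeks after radiotherapy recovers none of the missed episodes, since each has ended by week 6. With the boost in weeks 6-7, every missed episode of 2 or 3 weeks starts before the boost, when both arms have had the same planned treatment. Only an episode confined to week 6 is both missed and within the boost. If Table 1's timing applies, a 2-week episode starting in week 5 is also missed.

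**The case against.** Grading at set points is a legitimate design, and three scheduled grades come at the end of the boost or after it: week 7, 2 weeks after radiotherapy, and 3 months. For a boost in the last two weeks these are well placed to catch effects that persist. That stands.

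A reader might infer that peak toxicity goes ungraded. The documents do not support this: nothing in them says when toxicity peaks.

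A reader might also infer that the schedule pulls the toxicity comparison towards no difference. This is not shown either. On the text's timing, the missed 2- to 3-week episodes in the illustration all start before the boost and have no evident reason to differ by arm.

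It can further be said that weekly grading may already happen. The abstract can be read that way, and acting on grade 3 or higher implies that someone assigns a grade. Nor do the documents say whether a scheduled evaluation records the current grade or the worst since the last one; that detail may sit in the full protocol or the analysis plan, and its absence from the article is not a fault. These arguments limit what can be claimed about lost data. They do not remove the conflict between the abstract and the endpoint schedule, which the text and Table 1 state explicitly.

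**Conclusion.** The point stands as a schedule that is thinner than the planned visits allow and that sits badly with the abstract. On-treatment CTCAE grading is scheduled at 2 of 7 weekly reviews, the first of them before any boost on either timing. Toxicity confined to weeks 5-6, including a short episode early in the boost or one that resolves during a treatment break, has no scheduled grade, so the maximum acute grade may be underestimated.

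The 14% to 71% in the illustration rests on the assumed episode lengths, uniform starts and current-grade recording; it shows where the gaps lie and does not estimate the loss. The size and direction of any effect on the comparison of Arms 2 and 3 are not established. This is a low-cost improvement worth making, and it does not invalidate the endpoint.

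**What to change.** 1. Reconcile the abstract, the adherence section, the acute toxicity paragraph and Table 1 by marking CTCAE at each weekly review in weeks 1-7 for both randomised arms.
2. Analyse the worst CTCAE grade per patient over the acute period, and report separately the worst grade from the start of phase II. Anchor that second window to the same treatment point in both arms.
3. Settle whether month 6 belongs to the CTCAE schedule: Table 1 marks it, the text omits it.
4. Reconcile the boost timing, weeks 5-7 in Table 1 against weeks 6-7 in the Intervention text. The phase II window cannot be defined until the two agree.

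The cost is 7 − 2 = 5 extra CTCAE entries per patient, at most 5 × 124 = 620 over the planned randomised sample, at reviews already planned. The change concerns data collection only. Its limit is that recruitment has run since March 2024: patients already treated will have only the existing scheduled grades unless their weekly notes allow grading. The report should say which patients have weekly grades, by arm.

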## Sample size

Estimated LC rates 59% and 84% in the control and treatment arm, respectively, in the phase II study by Welz *et al* [29]. For achieving an 80% power (i.e., 1−β = 0.8) at the 5% level of significance (i.e., α = 0.05) with the equal allocation (i.e., k = 1), the sample size for Arm 2 and 3 is 62 patients in each arm. This study is designed as a Phase II trial aimed at evaluating the preliminary efficacy and safety of the intervention. As such, the primary focus is on detecting a signal of LRC rather than establishing a long-term survival benefit. The sample size of 124 participants (62 per group) is consistent with Phase II study designs, which typically involve smaller cohorts to efficiently assess early efficacy. Due to the exploratory nature of this trial, the follow-up period was set at 2 years to capture early control rates, which are increasingly recognised as predictive of long-term outcomes in salivary ductal cancers. The 2-year endpoint aligns with the study’s goal of generating data to inform the feasibility of subsequent Phase III trials.

### Data collection and analysis

All data will be collected in the central registry of the institute and anonymised. All statistical analyses were performed using the Statistical Package for Social Science System (SPSS v26, SPSS Inc, Chicago, IL) or equivalent software. Continuous variables will be written as mean (along with standard deviation) and median (along with interquartile range). Categorical variables will be represented as frequencies and percentages. Inter-cohort testing will be performed using chi-square for categorical variables and independent-t/nonparametric tests for continuous variables. Time-to-event endpoints will be measured from the date of randomisation to the date of failure or last follow-up. The LRC rate at 2 years will be estimated using the Kaplan–Meier method, with the time to locoregional failure defined as the duration from the start of radiation therapy to the first documented recurrence or progression within the primary tumour site or regional lymph nodes. The LRFS and OS, as mentioned earlier, death from any cause will be considered a failure. The LRFS and the OS rates will be estimated using the Kaplan–Meier product-limit method for each arm. Their distributions will be compared between treatment arms (Arms 2 and 3) with a two-sided log-rank test ≤ 0.05. The clinicopathological characteristics, survival outcomes and treatment modalities will be analysed using the univariate and multivariate Cox proportional hazards model. All eligible patients will be included in the analysis in the arm to which they were randomly assigned (intent-to-treat).

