Dysphagia assessment: Dysphagia is commonly evaluated through functional assessments of swallowing, such as videofluoroscopy or fiberoptic endoscopic evaluation. Furthermore, tools that quantify the severity and impact of dysphagia are essential for determining treatment outcomes and rehabilitation requirements. Various instruments are available for assessing dysphagia, including the 10-item Eating Assessment Tool [45], the Sydney Swallow Questionnaire [46], the Swallowing Quality of Life Questionnaire (SWAL-QOL) [47] and the MD Anderson Dysphagia Inventory (MDADI) [48]. The MDADI includes global, emotional, functional and physical subscales, each designed to capture different aspects of how dysphagia impacts quality of life. The global assessment question provides a straightforward method for evaluating overall dysphagia severity. It was specifically chosen because of its relatively shorter 20-point questionnaire and easier implementation, especially when compared to SWAL-QOL or dysphagia handicap index [49].

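### The only between-arm test stated for continuous outcomes is an unadjusted two-sample test; for the quality-of-life and dysphagia scores, a baseline-adjusted longitudinal model would use the collected data better

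*Protocol article*

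**What the plan says.** The protocol article's section Data collection and analysis describes how variables will be summarised and then gives a single sentence on comparing groups: "Inter-cohort testing will be performed using chi-square for categorical variables and independent-t/nonparametric tests for continuous variables". The other between-arm methods there are the log-rank test and Cox models, which apply to times to event and not to scores.

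The patient-reported outcomes are secondary. Under Secondary endpoints, the QLQ-C30 is described as "five functional scales that include physical, role, cognitive, emotional and social; three symptom scales", together with "a global QoL scale; and six single items". The H&N35 is described as "seven multiple-item scales that assess the symptoms of pain, swallowing ability" and further symptoms, plus "six single-item scales that assess the presence of symptomatic problems". The EORTC scores are quantitative: "All the scales of the EORTC QLQ-C30, QLQ-H and N35 range from 0 to 100". For dysphagia, "The MDADI includes global, emotional, functional and physical subscales".

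Table 1 has a row for "EORTC QLQ C30 and HN35" and an identical row for MDADI. Each is marked once at allocation, before radiotherapy, and then at weeks 4 and 7, at the second post-radiotherapy time point, and at months 3, 6, 12, 18 and 24.

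Under Arm allocation and randomisation, hypoxic patients are stratified by T stage, N stage and tumour site and then randomised 1:1 to Arm 2 or Arm 3.

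**The concern.** The design collects a baseline score and eight follow-up scores per patient on every scale. The one stated test compares two independent groups on one number per patient. Used on raw scores, it leaves out the baseline, which is often the strongest available predictor of a later score. Used visit by visit, it also leaves out each patient's other visits, and patients without a form at that visit do not contribute.

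The stake is precision on outcomes that matter here. The Objectives section frames the need as better locoregional control without loss of quality of life, and the Sample size section says the trial should inform later phase III work. With 62 patients per arm, imprecise quality-of-life comparisons would make it harder to see what the added dose costs patients. A secondary issue is that many scales and visits, each open to a test, leave room for chance findings.

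**Working it through.** **Plan's own figure.** The article gives no number of patient-reported comparisons and no power for them, so there is nothing to reproduce. The 62 per arm is taken as stated; it was set for locoregional control.

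**1. Power of the unadjusted test.** Inputs: n = 62 per arm (Sample size); two-sided 5% and 80% power (assumed for these outcomes, since the article states no significance level for them); complete data; normal approximation.

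- Standard error of the difference in SD units: √(2/62) = 0.1796.
- Difference detectable with 80% power: (1.960 + 0.842) × 0.1796 = 0.50 SD.
- Power for a 0.5 SD difference: Φ(0.5/0.1796 − 1.960) = Φ(0.824) = 79.5%.

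**2. Effect of baseline adjustment.** Let r be the correlation between baseline and follow-up score. The documents give no value, so r = 0.5 is assumed, with a range of 0.3 to 0.7. With equal variances at the two times, the variance relative to a raw-score comparison is 1 − r² for a baseline-adjusted comparison and 2(1 − r) for a change score.

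| Assumed r | Adjusted variance, 1 − r² | Change-score variance, 2(1 − r) | Detectable difference, adjusted | Power for 0.5 SD, adjusted |
|---|---|---|---|---|
| 0.3 | 0.91 | 1.40 | 0.48 SD | 83% |
| 0.5 | 0.75 | 1.00 | 0.44 SD | 90% |
| 0.7 | 0.51 | 0.60 | 0.36 SD | 97% |

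Example at r = 0.5: Φ(0.5/(0.1796 × √0.75) − 1.960) = Φ(1.255) = 89.5%. The variance gain equals a sample larger by 1/0.75 − 1 = 33%. At r = 0.3 it is 1/0.91 − 1 = 10%, and at r = 0.7 it is 1/0.51 − 1 = 96%.

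A t test on change scores does use the baseline, but its variance exceeds the adjusted variance at each value in the table. At r = 0.5 it gains nothing over raw scores, and at r = 0.3 it is worse.

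**3. Upper limit on the number of comparisons.**

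- QLQ-C30 as described: 5 + 3 + 1 + 6 = 15.
- H&N35 as described: 7 + 6 = 13.
- MDADI: 4.
- Total: 32 scores.
- Post-baseline times in Table 1: 8.
- Every score at every time: 32 × 8 = 256.

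At an assumed 5% for each test with no true effect, 256 × 0.05 = 12.8 false positives would be expected. Correlation between scales does not change this expectation. One test per scale over all visits would give 32 tests and 32 × 0.05 = 1.6. The article states neither approach.

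**The case against.** The strongest objection is that the sentence is generic. It names no questionnaire, no visit, no choice between raw and change scores and no handling of missing forms. It follows directly on the descriptive statistics and may mainly concern patient characteristics. A reader might infer that the article plans a separate test of each scale at each visit, ignores the baseline and so commits itself to 256 tests and about 13 false positives. The documents do not support that inference: 256 is a ceiling reached by testing everything everywhere, and no significance level is stated for these outcomes.

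Nor is the lack of a key scale or a multiplicity rule a finding in itself. Such details are commonly left to a full protocol or SAP, and neither is shown. The article calls the trial exploratory and promises no confirmatory quality-of-life claim.

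Further, an unadjusted two-sample test is valid in a 1:1 randomised comparison. Chance baseline imbalance is already covered by its type I error. Its 79.5% power for 0.5 SD is not poor, and the size of the gain rests on a correlation from outside the documents. The retention strategy, with telephone and video contact, is also meant to limit missing forms.

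All of this stands, and it reduces the point to one of efficiency. What remains is that this sentence is the only stated comparison that can cover these scores. If it is meant for them, a better method exists for data already being collected. If it is not, the article states no comparison for them, and a clarifying sentence is useful either way.

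**Conclusion.** The point holds as an improvement to a valid method, not as the correction of an error. Applied to the QLQ-C30, H&N35 and MDADI scores, the stated test would not use the repeated visits and, on raw scores, would not use the baseline. Running it on change scores removes only part of the loss.

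At 62 per arm, adjustment would raise power for a 0.5 SD difference from about 80% to about 90%, with a range of 83% to 97%. This rests on an assumed baseline correlation of 0.5 (0.3 to 0.7), equal variances, a two-sided 5% level and complete data. It describes one scale at one time. The ceiling of 256 comparisons shows why some order among the scales would help; it does not describe what the article plans.

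**What to change.** State that, for Arm 2 versus Arm 3, each patient-reported scale will be analysed with one repeated-measures mixed model containing baseline score, visit, arm, the arm-by-visit interaction and the stratification factors (T stage, N stage, tumour site). Report the arm differences as estimates with confidence intervals. The model also uses the available forms of patients who miss a later visit, on the assumption that forms are missing at random given the observed data. The two-sample sentence can stay for describing patient characteristics.

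As a supporting step only, name one or a few key scales and a time point before the data are reviewed, and treat all other scales and visits as descriptive.

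The cost is a change of wording and slightly more modelling. Fewer scales could carry a formal claim. No extra patients, visits or forms are needed, and the article reports that recruitment is still open.

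### On either clock in the analysis section, the last scheduled disease assessment falls after the 24-month point at which LRC is read, so recurrences first documented there miss the primary 2-year rate

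*Protocol article*

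**What the plan says.** The protocol article gives three time origins for locoregional control (LRC):

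- **Start of radiotherapy.** Data collection and analysis: "The LRC rate at 2 years will be estimated using the Kaplan–Meier method, with the time to locoregional failure defined as the duration from the". The origin that this sentence goes on to name is RT start.
- **Randomisation.** The same section: "Time-to-event endpoints will be measured from the date of randomisation to the date of failure or last follow-up". The abstract agrees, with LRC "defined as the time from randomisation to the first histopathologically confirmed relapse of locoregional disease".
- **End of treatment.** The primary endpoint paragraph (under Adherence to protocol and concomitant care): "LRC will be assessed at predefined time points, with the primary time point being 2 years post-treatment".

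Table 1 sets the visits. The row "Response assessment (Clinical ± radiological") is marked at months 3, 6, 12, 18 and 24. The last three stand under the column group "Late phase (Post RT"), so they are counted from the end of radiotherapy. Month 24 is the last. Randomisation is placed before radiotherapy. The Intervention section describes 5 weeks of treatment followed by 2 more, and Table 1 shows seven treatment weeks for every arm.

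**The concern.** The 2-year LRC rate is the primary result, and a Kaplan–Meier rate at 24 months counts only failures dated by then. If the clock starts at RT start or earlier while visits are counted from the end of RT, the visit meant to establish 2-year status comes after the reading. A recurrence that arises after the month-18 visit and is first documented at the month-24 visit is then counted as controlled.

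This overstates control in both arms. Under the planning rates it also shrinks the difference, because the arm with more failures loses more events. The error works against the trial's own hypothesis and does not create a false-positive risk.

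**Working it through.** **Plan's own figure.** The article gives no figure for this effect. Its nearest figure is 62 per arm, from 59% v 84%, 80% power and 5% significance. The usual two-sided comparison of two proportions gives 50 per arm, or 58 with continuity correction, so 62 is not reproduced. The timing point does not depend on it; 62 is used below only to compute power.

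**Visit times**

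- RT duration: 7 weeks = 49 days; 49 / 30.44 = 1.61 months.
- Month-18 visit, from RT start: 18 + 1.61 = 19.61 months.
- Month-24 visit, from RT start: 24 + 1.61 = 25.61 months.

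| Clock | Month-24 visit falls at | Gap past the 24-month reading |
|---|---|---|
| RT start | 25.6 months | 1.6 months |
| Randomisation | later than 25.6 months | 1.6 months plus the unstated wait for RT |
| End of treatment | 24.0 months | 0 |

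**Size on the RT-start clock.** Assumptions: 59% and 84% are the true 24-month rates, and the hazard is constant. Let f be the share of recurrences arising after the month-18 visit that are found only at scheduled visits.

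- LRC at the last scheduled look before 24 months is S(19.61) = S(24)^(19.61/24).
- Control arm: 0.59^0.817 = 0.650. Dose-escalated arm: 0.84^0.817 = 0.867.
- Rate read at 24 months = S(24) + f × [S(19.61) − S(24)].
- Power = Φ{ [d√n − 1.96√(2p̄(1−p̄))] / √[p₁(1−p₁) + p₂(1−p₂)] }, where n = 62, d is the difference and p̄ the mean of the two rates. At f = 0: (1.969 − 1.251) / 0.613 = 1.17, so power is 87.9%.

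| f | Rates read | Difference | Events missed per 62 (control, escalated) | Power |
|---|---|---|---|---|
| 0% | 59.0% v 84.0% | 25.0 points | 0, 0 | 87.9% |
| 50% | 62.0% v 85.4% | 23.4 points | 1.9, 0.8 | 84.9% |
| 100% | 65.0% v 86.7% | 21.7 points | 3.7, 1.7 | about 81.5% |

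**Other failure patterns, f = 100%**

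- *Front-loaded failures* (75% in year 1, the rest uniform to 24 months). The share dated by 19.61 months is 0.75 + 0.25 × 7.61/12 = 0.909. The rates are 1 − 0.41 × 0.909 = 62.7% and 1 − 0.16 × 0.909 = 85.5%, a difference of about 23 points.
- *59% and 84% taken as 5-year rates.* The sample size section gives no time point, and the rationale section describes the source trial's result as 5-year local control. At 24 months: 0.59^0.4 = 81.0% and 0.84^0.4 = 93.3%, a difference of 12.3 points. At 19.61 months: 0.59^0.327 = 84.2% and 0.84^0.327 = 94.5%, a difference of 10.3 points. The loss is about 2 points.

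**The case against.** The strongest reply is that the paragraph defining the primary endpoint sets the time point at 2 years after treatment. That matches Table 1 exactly, and on that clock nothing is lost if the visit and its documentation fall on the due date. This stands. The gap follows from the two clocks in the analysis section, not from every reading of the article.

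A reader might infer that aligning the clock cures nothing, so that the reported rate is a 20-month rate whichever origin is chosen. The documents do not support that. On the post-treatment clock, only visits or confirmations after the exact date are lost. Visit windows are commonly left to the full protocol or SAP, so their absence from an article is not a finding. A thinner point remains: the abstract requires histological proof of relapse, and the response assessment text allows repeat imaging before biopsy. A finding from an on-time visit could therefore be confirmed after the reading point.

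It is also fair that the 22-point figure is a ceiling. The article does not restrict detection to scheduled visits, and recurrences documented between visits before 24 months count as they should. Later events stay on the Kaplan–Meier curve and in any test of the whole curve. That limits the harm to the 24-month rate, but this is the summary the article names for LRC; its log-rank sentence follows the text on LRFS and OS.

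**Conclusion.** The point holds in limited form. On both clocks in the analysis section, the final scheduled assessment lies at least about 1.6 months after the reading point, so recurrences first documented there drop out of the primary 2-year rate. This is a conflict between stated rules, not missing detail.

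The effect is modest. At most the reading becomes 65% v 87% (22 points instead of 25), given a constant hazard, planning rates that hold at 24 months, and no late recurrence found between visits. With half found between visits it is 62% v 85% (about 23 points). Power with 62 per arm stays above the planned 80% in both cases. On the post-treatment clock the loss is zero apart from late visits and late confirmation.

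**What to change.** Reconcile the abstract, the primary endpoint paragraph and the analysis section to one time origin for LRC. Then add a sentence: a locoregional failure first found at the month-24 post-RT assessment, within a stated window and including later confirmation of a finding from that visit, counts as an event in the 2-year rate. One way is to place both events and censorings from that visit at its nominal 2-year time, identically in both arms.

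Moving the reading to a later time such as 27 months is not advisable. Follow-up is set at 2 years, and controlled patients are last seen at about 25.6 months from RT start. The risk set would collapse around that visit, and failures dated late within it would carry too much weight.

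The cost is an edit to the endpoint and analysis text, with no new visits. Reported LRC will be slightly lower in both arms. The article describes recruitment as ongoing, so this can be settled before 2-year outcomes mature.
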